### Subgroup analysis

In addition to our analysis of overall CCB exposure, the analysis for each aim will be conducted separately according to CCB class (ie, dihydropyridines and non-dihydropyridines) and duration of action (ie, short or long action) where sufficient statistical power exists. Moreover, we will conduct a subgroup analysis to assess the influence of a personal history of any cancer at cohort entry on the risk of breast cancer and CCB exposure.

### Sensitivity analyses

We will conduct several sensitivity analyses. Since hyperplasia and atypical lesions are not precancerous, we will test the effect of adding ductal carcinoma in situ as a competing risk in sensitivity analyses rather than as an exclusion criterion. We will explore the impact of imposing various time lags, based on clinical consultation, between the start of follow-up on the outcome to account for latency and plausible timing between exposure and outcome development. The potential impact of reduced exposure resulting from imperfect adherence and prescribing at defined daily dose levels (a statistical measure of drug consumption, defined by the WHO) will be investigated in the dose-duration models and through sensitivity analyses.^36^ We will expand the study population to women with prior CCB use at entry (captured as a starting dose-duration value using available look-back data) to examine the impact of CCB use (overall) on the outcome. Finally, because concessional status for subsidised medicines in Australia can change with age or employment status, we will explore varying the definition of continuous PBS concessional status in Australian women to determine the impact this has on the association of CCB exposure with the outcome. The main analysis for the study will be evidence of 100% concessional status between 2003 and 2012 with a single year of no evidence allowed (ie, at least one dispensation per year, and patient recorded as being on concessional status on each dispensation, with 1 year allowed to vary). This will be varied allowing 2 years of no evidence (the more relaxed scenario) and requiring 100% concessional status across all years (as the most stringent requirement). Sensitivity analyses will be applied to the primary aim in the first instance, and those factors found to be influential will be additionally tested in the secondary aim. Due to the potential duplication of participants who were part of the ALSWH and also enrolled in the 45 and Up Study residing in NSW, we will systematically exclude ALSWH participants residint in NSW in a sensitivity analysis. This exclusion is essential for evaluating the potential impact of duplication on the study results.

### Sample size calculation

Breast cancer is a relatively common event for the studies under investigation; thus, our sample size will be based on the women exposed to CCBs (as indicated by the numbers on the right-hand side of figure 3). Using a conservative ratio of unexposed:exposed of 5:1, we have 95% confidence with 80% power to detect a minimum effect size of ±0.2 for breast cancer associated with CCB use in all datasets given the number of exposed individuals.

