### Study population

The same study population will be used for the primary and secondary aims. Entry to our study will be on survey completion date for women who participated in the ALSWH survey waves between 2004 and 2008 or the 45 and Up Study baseline survey between 2006 and 2009 or the date of the Rotterdam Study interview and clinical examinations for women who completed these between 2004 and 2008. Inclusion criteria will be women who at entry to our study (1) were alive and consented to linkage of administrative data, (2) have evidence of hypertension from either self-reported hypertension (Australian longitudinal cohorts) or have a recorded diagnosis of hypertension in clinical examination data (Rotterdam cohorts).

Women will be excluded at entry if they had (1) history of primary invasive/in situ breast cancer or cancer that is metastatic to the breast; or (2) history of bilateral mastectomy; or (3) evidence of CCB use prior to entry. Further exclusion criteria will be applied in Australian longitudinal cohorts only as per standard practice when using PBS data: (1) women with any evidence of being Department of Veterans’ Affairs (DVA) concession card holders, because DVA-subsidised prescriptions are funded separately and not captured in the PBS data held; or (2) women who did not have evidence of concessional healthcare status for more than 1 year during period from 2003 to 2012. Those with concessional status, for example, those receiving the aged care pension or certain other government benefits, have lower copayments for PBS-listed medicines in comparison to ‘general beneficiaries’. This exclusion is necessary because some AHT medicines fall below the PBS copayment threshold for general beneficiaries, hence attracted no government reimbursement and were not captured in PBS data prior to an administrative change in 2012.^30^ In contrast, the lower copayment threshold for concessional patients means that AHT medicines can be captured throughout the study period.

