### Exposure ascertainment

The exposure in this study, for both the primary and secondary aims, will be CCB dispensing including both combination and monotherapy products. Exploring the impact of confounding by indication for non-CCB AHT medicines is important because a modest increased risk of cancer in individuals with hypertension has been documented.^33^ To avoid this issue, previous studies have used a comparator group of patients exposed to other AHTs and/or with a hypertension diagnosis.^34^ Our study population is defined by the presence of hypertension since comparing only to a reference AHT medicine group risks biasing towards the null, if the comparator drug is associated with the outcome. Thus, to reduce bias to the null, women who are both AHT and CCB naïve will be included in the study as long as they meet the entry criteria of hypertension at baseline as described previously. To ensure that exposure to other AHT medicines is accounted for, the cumulative dose-duration exposure of other prescribed AHT medicines (combined) will be captured in the same way as that described for CCB exposure. Thus, in our study, the following four exposure states will be possible during follow-up: (1) women with no exposure to either CCBs or other AHTs; (2) women exposed to other AHTs but not exposed to CCBs; (3) women exposed to CCBs but not exposed to other AHTs and (4) women exposed (at any time) to both CCBs and AHTs. To compensate for immortal-time bias, and to be able to capture the dose–response nature of the association of CCB exposure with risk of breast cancer, a time-varying continuous ascertainment of cumulative exposure (dose duration) to CCB (and separately other AHTs) will be captured as follows.^35^

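### The 80% power claim counts women ever exposed to CCBs at 5:1, but the primary exposure starts at zero and varies over time, so the calculation overstates the information available

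*Protocol article*

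**What the plan says.** The Sample size calculation section argues that "Breast cancer is a relatively common event for the studies under investigation" and that, for this reason, "our sample size will be based on the women exposed to CCBs". The ratio is introduced with the words "Using a conservative ratio of unexposed:exposed of 5:1". At 80% power and 95% confidence, the authors then say they are able "to detect a minimum effect size of ±0.2 for breast cancer associated with CCB use". They make this claim for every cohort, not only the largest: "in all datasets given the number of exposed individuals". The unit is the individual woman. The text gives no event count, no exposed count and no scale for ±0.2. Figure 3, which carries the numbers exposed, is not shown.

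Two other sections define what the primary analysis compares. Under Study population, a woman is excluded if there is "evidence of CCB use prior to entry", so everyone enters unexposed. Under Exposure ascertainment, the exposure is "a time-varying continuous ascertainment of cumulative exposure (dose duration) to CCB", chosen to deal with immortal-time bias. The Statistical analysis section adds that exposure is expected to be intermittent, and plans a propensity-matched comparison of exposed and non-exposed women alongside the dose-duration model.

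**The concern.** A ratio of 5:1 in women is also 5:1 in follow-up only if exposed women are exposed from entry. Here none are. Each woman counted as exposed has a period before her first CCB dispensing, and a time-varying analysis places that period on the unexposed side. Any breast cancer diagnosed in it counts against non-use. The contrast is therefore more unbalanced than the calculation assumes, and carries less information for the same women and events.

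The stated detectable effect matters because the study may well report no association. The closing paragraph of the Discussion says such a result would reassure women that CCBs add no breast cancer risk. That reassurance depends partly on which effect sizes the study could have detected. If the planning figure is too favourable, a null result will be read as excluding smaller effects than it can.

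**Working it through.** **Inputs from the article.** 95% confidence, taken as two-sided α = 0.05; power 80%; effect ±0.2; ratio 5:1, so a headcount exposed share of 1/6.

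**Assumptions.** The ±0.2 is read as a hazard ratio of 1.2 or 0.8. The share *s* of an ever-exposed woman's follow-up that comes after initiation is not given, so a range is used. Ever-exposed and never-exposed women are taken to be followed for similar lengths of time. All time after the first dispensing counts as exposed, because cumulative exposure does not return to zero when treatment stops.

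**Step 1: the plan's own figure.** It cannot be reproduced, because neither events nor exposed counts are in the text. The Schoenfeld formula gives what the inputs imply: D = (1.96 + 0.8416)² / [p(1 − p)(ln HR)²] with p = 1/6. This is 1,701 events for HR 1.2 and 1,135 for HR 0.8. The check below starts from a dataset with exactly these events, that is, exactly 80% power on headcount.

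**Step 2: move pre-initiation time to the unexposed side.** Women and events stay the same; only the exposed share changes, from 1/6 to p = s/6. Information is proportional to p(1 − p). On headcount this is 1/6 × 5/6 = 0.1389. Relative information is R = p(1 − p)/0.1389, power is Φ(2.80√R − 1.96), and the effect detectable at 80% is about 0.2/√R.

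| s | p | R | Power | Detectable effect |
|---|---|---|---|---|
| 0.90 | 0.150 | 0.918 | 77% | 0.21 |
| 0.75 | 0.125 | 0.788 | 70% | 0.23 |
| 0.60 | 0.100 | 0.648 | 62% | 0.25 |
| 0.50 | 0.083 | 0.550 | 55% | 0.27 |
| 0.40 | 0.067 | 0.448 | 47% | 0.30 |
| 0.25 | 0.042 | 0.288 | 32% | 0.37 |

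At s = 0.5, for example, p(1 − p) = 1/12 × 11/12 = 0.0764 and R = 0.0764/0.1389 = 0.55. Then z = 2.80 × √0.55 = 2.08 and power = Φ(0.12) = 0.547. Restoring 80% would take 3,092 events instead of 1,701 (HR 1.2), or 2,064 instead of 1,135 (HR 0.8), about 1.8 times as many.

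**Step 3: does the scale of ±0.2 matter?** Hardly. With a standardised difference of 0.2, s = 0.5 also gives 54.7%. With two proportions at assumed risks of 2% to 5%, it gives about 53% to 56%.

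**Step 4: can a larger unexposed group make up the loss?** With the number of exposed women fixed and k unexposed per exposed woman, information is proportional to s(1 − s/(1 + k)). The plan's case, s = 1 and k = 5, gives 0.833. At s = 0.5, power is 56% at 10:1 and 58% with unlimited unexposed women (R = 0.5/0.833 = 0.60). At s = 0.75 the ceiling is 76%. Even with unlimited unexposed women, 80% is reached only if s is at least 0.833.

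**Step 5: what if there are more exposed women than 5:1 implies?** With total events held fixed and s = 0.5, power is 62% at 4:1, 70% at 3:1 and 80% at 2:1. A surplus of exposed women can therefore absorb the loss.

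**The case against.** The strongest objection is that the size of the effect is unknown. No section gives the time to first dispensing, Figure 3 is not shown, and 80% may be a floor. The Data sources section describes very unequal studies: 267,357 participants in the 45 and Up Study, 53.6% of them women, against 14,926 of both sexes in the Rotterdam Study. If the claim holds in the smallest dataset, the largest may have power to spare. The article also calls 5:1 conservative, which may mean that the real ratio has relatively more exposed women; step 5 shows that this could offset part or all of the loss. These points stand. A reader might infer from the table that the study has 55% power, that every dataset misses 80%, or that the word conservative is wrong. The article supports none of these.

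A second objection is that headcount fits the matched exposed-versus-non-exposed comparison, and that the Abstract and parts of Exposure ascertainment describe exposure totalled at exit. But the matched comparison is an added baseline analysis, the power claim is not limited to it, and the article says explicitly that the exposure is time-varying in order to deal with immortal time. If the calculation was meant for the matched comparison only, it should say so.

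Third, the p(1 − p) formula covers a binary contrast. Power for the model with duration, dose and their interaction depends on the variance of cumulative exposure, which is not given. This stands: the figures above say nothing about that model, and neither does the plan's 80%.

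Fourth, the data already exist, cohort estimates will be pooled, and results from insufficient samples will be labelled exploratory. This limits the consequence but does not correct the stated figure, which is claimed for all datasets. An article may leave detail to a fuller document, but the basis it does state, women exposed at 5:1, does not match its own primary exposure.

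**Conclusion.** The concern holds in direction and is conditional in size. The calculation counts women ever exposed, while the primary analysis starts every woman unexposed and lets exposure accrue over time. If 5:1 is the ever-exposed ratio and follow-up is of similar length in both groups, the exposed share of follow-up is below 1 in 6 and the stated 80% overstates the information in the primary analysis. No outside figure is needed for that.

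The amount depends on the post-initiation share. For a binary ever-started contrast in a dataset that just reaches 80% on headcount at 5:1, power runs from about 32% (share 25%) to 77% (share 90%). It is about 55%, with a detectable effect of about 0.27, at a share of one half. That middle case is an illustration, not an estimate for this study, and a dataset with enough surplus exposed women may still reach 80%.

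**What to change.** Recompute the Sample size calculation section for each dataset, with the exposed fraction equal to post-initiation person-time divided by total person-time. The dispensing dates needed are already held for all cohorts. In the revised text:

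- state the scale of ±0.2 (hazard ratio, risk ratio or standardised difference);
- restate the power at ±0.2, or the effect detectable at 80%, for each dataset;
- say that the figure applies to an ever-started contrast and not to the dose-duration model;
- keep the description of 5:1 as conservative only if the recalculation supports it.

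The cost is one recalculation from existing data and possibly a less favourable stated figure. No design change or new data collection is needed.

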**Figure 3 F3:**
[figure not shown]
Sample size calculation.

### Individual patient data meta-analysis

For the primary aim, a two-step (since the data cannot be brought together) random effects individual patient-level meta-analysis which allows for assessment of effect modification (ie, interaction terms) by country or personal characteristics will be undertaken.^56^ First, each individual study estimate will be calculated, plotted using a forest plot and compared with observe any similarities and differences. Next, individual estimates will be weighted using the Knapp‐Hartung method and pooled using random effects methods taking into account both within and between variance as follows^57^:

### Patient and public involvement

There was no patient or public involvement in the design of the proposed study.

### Ethics and dissemination

Ethical approval was obtained from the following Human research Ethics Committees: Curtin University (HRECs) (ref No. HRE2022-0335), NSW Population and Health Services Research Ethics Committee (2022/ETH01392/2022.31), ACT Research Ethics and Governance Office approval under National Mutual Acceptance for multijurisdictional data linkage research (2022.STE.00208). For the ALSWH survey collections, ongoing ethical approval has beengranted by the HREC of the Universities of Newcastle and Queensland (approval numbers H076-0795 and 2004000224, respectively). The ALSWH also maintains institutional HREC approvals for external record linkage (approval numbers H-2011-0371 and 2012000132, respectively). In addition, access to national collections which include MBS/PBS, National Death Index, Australian Cancer Database is approved by the Australian Institute of Health and Welfare. Access to state and territory data collections which include hospital admissions and cancer registries is approved by an appropriate HREC for each jurisdiction.^58^ These data are approved by individual ethics committees and custodians in different jurisdictions, though the researchers make a single application to the ALSWH Data Access Committee, who then contact individual custodians on behalf of researchers. The Rotterdam Study data have been approved by the Medical Ethics Committee of the Erasmus MC (registration number MEC 02.1015) and by the Dutch Ministry of Health, Welfare and Sport (Population Screening Act WBO, license number 1071272–159521 PG). The Rotterdam Study Personal Registration Data collection is filed with the Erasmus MC Data Protection Officer under registration number EMC1712001.

Each of the studies collected informed consent from all participants at recruitment. Women who participated in earlier waves of the ALSWH provided consent for access to administrative health data including the MBS, PBS, national death index, cancer registries and hospital records for most Australian States and Territories. In later waves, there has been a change to opt-out consent of these linkages, with participants provided information on the datasets that may be linked and a freecall phone number to opt out provided to participants at recruitment and in an annual newsletter. All study participants in the 45 and Up study consented to their survey data being linked to routinely collected health administrative data and health registry sources. All participants in the Rotterdam Study provided written informed consent to participate in the study and to have their information obtained from treating physicians.

Results of the proposed study will be published in high-impact journals and presented to key stakeholders via scientific meetings, lay press (print media, television, radio and internet).

## Discussion

The equivocal literature regarding the potential association between CCB exposure and breast cancer is likely due to differences in study design (eg, cohort vs case control), length of follow-up, exposure measurement (eg, ever vs never or time duration) or population characteristics (eg, patients with hypertension and/or cardiovascular disease vs general population cohorts, which have differing risk of confounding by indication). These differences, along with small sample sizes in many studies (often n<1000), make inference difficult. Randomised, controlled trials are not usually suitable for identifying long-term adverse effects of medicine use and long-term monitoring through observational studies using administrative datasets has become the standard way of overcoming this limitation for postmarket surveillance research.^59^ However, the sole use of administrative data limits the ability to control for critical lifestyle and other potential confounding factors that are not routinely reported in such datasets, for example, BMI, physical activity, smoking and alcohol use history. In many studies, longitudinal cohorts have been used to alleviate this issue but often these studies have suffered from reporting and/or recall bias due to the reliance on self-report data, especially regarding the determination of exposure relating to prescription medication use. This has led to the preponderance of crude ever/never exposed to CCBs in the literature rather than more complex dose-duration measures that we propose.

Our study will involve six longitudinal cohorts of women extracted from internationally renowned Australian and Dutch studies linked with administrative health data, with complete coverage, to allow for continuous capture of CCB exposure for an extended period of time (ie, up to 19 years). Using state-of-the-art analytical techniques such as dose-duration methods previously unused in this area, this study will evaluate the association and characterise the dose–response nature of any such association between long-term CCB use and the risk of breast cancer. A wide range of person-related, temporal-related and geospatial level-related factors will be measured and adjusted to separate the effect of these factors from the relationship between CCB use and breast cancer. The analytic methods (non-linear threshold modelling) proposed are novel and will be a significant innovation to pharmacoepidemiological analyses, which currently lack such sophisticated methods.

Due to the nature of the observational study design, confounding by indication will be unavoidable. To minimise the impact of this issue, the study will be limited to participants with a diagnosis/self-reported hypertension and comparisons will include participants exposed to other prescribed (non-CCB) AHT medicines in addition to those who have no pharmacotherapy for hypertension. As explained in the methods, the Australian cohorts will be restricted by concessional status to capture the AHT exposure over the study duration, and our study is therefore likely prone to selection bias; this will be investigated in the sensitivity analyses. Complete ascertainment of prior exposure will not be possible since we will not have lifetime capture of prescribing data; therefore, CCB exposure may be under-reported. Due to the nature of medicine dispensing data, the level of certainty regarding whether the dispensed medicine (eg, combined hormonal contraceptives, combined menopausal hormone therapy and CCB/AHT medicines) was consumed by the patient is unclear. The diagnostic interval of breast cancer may vary between Australian and Dutch women, particularly since case ascertainment through cancer registries can take months from the initial diagnosis to coding notifications. Previous studies have shown a difference around 30 days in the diagnostic interval days depending on the presentation of symptoms and the temporal differences in diagnostic pathways between the two countries.^60^ Another limitation is the absence of genetic data for this analysis. However, recent studies have indicated no association between genetic proxies for CCB or other antihypertensives and breast cancer through Mendelian randomisation study design.^61 62^

While we have used the term ‘association’ here, our use of GPS adjustment provides a mechanism for undertaking analysis under a causal framework. Modelling each woman’s propensity to receive the exposure as a function of covariates means that the GPS is independent of the outcomes and the study represents a quasi-experiment. We prefer to use the terminology ‘association’ when reporting our results so as not to overstate our ability to adjust for potential confounding. Interpretation of any association will incorporate the likelihood of causation (using the Bradford-Hill criteria).^63^

With regards to representativeness and generalisability of our results, leading epidemiologists^64^ and reputable peer-reviewed publications^65 66^ support the principle that cohort studies rely on the validity of internal comparisons to avoid systematic error and need not be a random sample of a larger population to provide generalisable knowledge. The validity of generalisation (ie, external not internal validity) depends on considerations about risk stratification and effect modification rather than bias/confounding. Thus, results of well-respected international cohort studies, such as the British Doctors’ Study and US Nurses’ Health Study, are regarded as providing generalisable knowledge despite their highly selected study samples.

The literature continues to debate whether or not CCBs increase the risk of breast cancer. The outcomes of the proposed study are likely to have considerable implications for both clinical practice and public health. If a positive association is found, this could have a global impact on clinical guidelines for treating hypertension in women. Long-term CCB use has the potential to become the number one major modifiable risk factor for breast cancer. Conversely if no association is found, this would provide reassurance to Australian and Dutch women that the current guidelines promoting CCBs as a first-line therapy for hypertension are appropriate and that taking a CCB does not pose additional breast cancer risk.

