In 2017, we published a systematic review and meta-analysis^15^ highlighting the uncertainty regarding the association between long-term use of CCBs and breast cancer, primarily due to the limited availability of long-term follow-up data. This review and meta-analysis found that the literature is equivocal on whether CCBs are a risk factor for breast cancer. Li *et al*
16 reported that long-term (>10 years) use of CCBs was associated with a 2.4-fold (95% CI 1.2 to 4.9) increased risk of invasive ductal breast cancer and 2.6-fold (95% CI 1.3 to 5.3) increased risk of invasive lobular breast cancer. In contrast, Grimaldi-Bensouda *et al,*
17 using data from the UK, and Wilson *et al*,^18^ using data from the USA, from sisters with and without breast cancer failed to find an association between CCB use and breast cancer (OR 0.95 (95% CI 0.87 to 1.04) and HR 0.88 (95% CI 0.58 to 1.33), respectively). A similar pattern was observed in a recent study conducted by Rotschild *et al* (2022) in Israel, revealing an OR 0.997 (95% CI 0.962 to 1.034) for a long-term exposure to CCBs (above 8 years) and breast cancer risk.^19^ A non-significant association was found in US women aged 55+ years for CCB use but a protective effect for ACEI use.^20^ However, a study by Gómez-Acebo *et al*
21 using Spanish data found CCB use for 5 or more years was associated with a 1.77 times increased risk (95% CI 0.99 to 3.17) of breast cancer. A 2021 systematic review of clinical trials showed no strong effect of any type of AHT medicine on breast cancer with a median follow-up of 4.2 years. However, a systematic review of cohort studies with longer follow-up (≥10 years) published in the same year found that the use of beta blockers, CCBs and diuretics was associated with increased breast cancer risk.^22^ The authors noted the heterogeneity of study design, study duration and capture of drug exposure status and also that most studies were from Europe or North America, limiting external validity.

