### Outcome ascertainment

During follow-up, incident diagnoses of invasive breast cancer will be identified using the International Classification of Diseases (ICD) version 10 Australian Modification^40^ for the Australian cohorts and the ICD-10^41^ for the Rotterdam Study. ICD-10 code C50.x (malignant neoplasm of breast) will be used to identify invasive breast cancer diagnosis across cancer registries and hospital admission data. In situ breast cancer (eg, D05.x) will not be included in the outcome because hyperplasia and atypical lesions are not precancerous (although some are risk factors), and only some ductal carcinoma in situ are obligate precursors.^42 43^

Cancer registries for all cohorts contain, by statutory requirement, records of all cancers diagnosed or treated and are therefore considered internationally the ‘gold standard’ for cancer identification for research purposes. Since cancer diagnoses for Dutch women and cancer registry data for the Australian women are only currently available until 2016 and 2018 respectively, breast cancers diagnosed later than these dates will be identified from GP data (Dutch women) and hospital data (Australian women). Hospital-derived diagnoses for breast cancer have a positive predictive value and sensitivity of 86% and specificity of 99.9% compared with the cancer registry in the 45 and Up Study population.^44^ Sensitivity analyses showed that 53% of women with a cancer registry diagnosis had an inpatient diagnosis within the same calendar month and 93% within one calendar month; thus, estimations of date of diagnosis align well with Cancer Registry dates.

The date of breast cancer diagnosis used in the study will be the date of diagnosis recorded in either the Australian Cancer Registry or the Rotterdam Study, or the date of the first hospital admission with a principal diagnosis of breast cancer/date recorded in the GP data where registry/study data are unavailable.

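### A null result would be read as reassurance at any duration of CCB use, although use beyond 10 years is a minority of exposed time in the main analysis and no precision is stated for it

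*Protocol article*

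**What the plan says.** The stated aim is long-term CCB use and its dose-response relation with breast cancer. The Introduction attributes the present uncertainty mainly to a lack of long follow-up. The strongest positive result it cites is that "long-term (>10 years) use of CCBs was associated with a 2.4-fold (95% CI 1.2 to 4.9) increased risk of invasive ductal breast cancer"; the matching figure for lobular cancer is 2.6-fold. It also cites a 1.77-fold estimate (0.99 to 3.17) for use of 5 years or more.

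Under Study population, entry falls in 2004-2008 (ALSWH, Rotterdam) or 2006-2009 (45 and Up). Women are excluded for "evidence of CCB use prior to entry", so cumulative use starts at zero at or after entry.

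Under Outcome ascertainment, registry data are "only currently available until 2016 and 2018 respectively" for the Dutch and Australian women. Later cases come from GP and hospital data. Data sources gives Rotterdam dispensing records to 2018. The Discussion speaks of exposure capture for up to 19 years.

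Two planned analyses could reach longer use. Under Sensitivity analyses: "We will expand the study population to women with prior CCB use at entry", with look-back use as the starting value. Under Covariates, earlier entry will be explored where possible in the cohort-specific analyses.

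The closing paragraph of the Discussion states: "Conversely if no association is found, this would provide reassurance to Australian and Dutch women". It treats such a finding as showing that "taking a CCB does not pose additional breast cancer risk".

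**The concern.** The conclusion is wider than the main analysis can carry. If risk rises only after about 10 years of use, an analysis dominated by shorter use can return an overall null without having tested the range that prompted the study. The Discussion would then offer women and guideline writers a safety statement that covers that range.

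Nothing else in the article closes the gap. The power statement concerns CCB use as a whole. The limitations mention unseen prior exposure, but not the shortening of observable use that follows from excluding prior users. No confidence limit is named that a null result must meet before it counts as reassurance.

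**Working it through.** **The plan's own figure.** Sample size calculation gives a detectable effect of ±0.2 at 95% confidence and 80% power with a 5:1 unexposed:exposed ratio. The scale is not stated and the exposed counts are in a figure that is not shown, so it cannot be reproduced. It refers to any CCB use, not to use beyond 10 years.

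**Inputs.** The entry windows, the registry end dates (2016, 2018) and the Rotterdam dispensing end (2018) are from the article. The end of Australian data is not given. I assume end-2022 as the extended case; from the start of 2004 that is 19 years, which agrees with the Discussion's maximum. Assumed: even entry over the window, CCB starts even over follow-up, no stopping and no death.

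**Formula.** For follow-up F and a start uniform on (0, F), attainable use is uniform on (0, F):
- share of starters who pass T years = (F − T)/F
- share of exposed time beyond T = ((F − T)²/2F) ÷ (F/2) = ((F − T)/F)²

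The time share is then averaged over entry dates, as mean[(F − T)²/2F, zero if F < T] ÷ mean[F/2]. Example: 45 and Up to end-2018 has F from 9 to 13 years, mean 11. At F = 11 the share beyond 10 years is (1/11)² = 0.8%; averaged over entry it is 1.7%.

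| Cohort, data end | Mean F (y) | Starters passing 10 y | Exposed time >10 y | Exposed time >5 y |
|---|---|---|---|---|
| Rotterdam, end-2016 | 10.5 | 8% | 1.4% | 28% |
| Rotterdam, end-2018 | 12.5 | 19% | 4.9% | 36% |
| 45 and Up, end-2018 | 11.0 | 9% | 1.7% | 30% |
| ALSWH, end-2018 | 12.5 | 19% | 4.9% | 36% |
| 45 and Up, end-2022 (assumed) | 15.0 | 33% | 11% | 44% |
| ALSWH, end-2022 (assumed) | 16.5 | 39% | 16% | 49% |

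**Sensitivity to the assumptions.**
- Stopping at an assumed 10% per year lowers the >10-year shares to 0.8-2.3% (2018 end) and 5-8% (2022 end).
- Starts at an assumed constant 5% per year, which come earlier in follow-up, raise the 2022 shares to 13-19%.
- If every user started on the day of entry, the share is (mean F − 10)/mean F where all follow-up reaches 10 years: 5/15 = 33% (45 and Up) and 6.5/16.5 = 39% (ALSWH) for 2022. It is about 9-20% at the registry end dates.

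**What this means for precision.** With Schoenfeld's formula, events = (1.96 + 0.84)² / [p(1 − p)(ln HR)²], where p is the share of all person-time in the exposed state (approximate for time-varying exposure). At HR 2.4 the need is 74 events for p = 1/6 (the 5:1 split). It is 304, 523 and 1,035 events for assumed p = 3.5%, 2% and 1% beyond 10 years. At HR 1.2 it is 1,701 events at 5:1 and 23,851 at p = 1%. The number of cases available is not given in the text, so these figures show only that the overall power statement does not carry over to long use.

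**The case against.** A reader might infer that the study has almost no exposed time beyond 10 years. The documents do not support that. Registry end dates do not close follow-up, because GP and hospital data continue case finding, each woman's end date depends on her available data, and exposure capture of up to 19 years is claimed. With an assumed 2022 end, the Australian shares are 11-16% and could be higher if starts cluster early. The description fits Rotterdam and any cohort cut at 2018.

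A reader might also infer that the prior-user sensitivity analysis is the only route to longer use. It is not: earlier entry is to be explored, and Rotterdam dispensing records begin in 1991. Nor is the motivating evidence confined to more than 10 years; the signal at 5 years or more lies in a range that the cohorts cover reasonably well.

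It can further be said that the main model is built around duration. It has cumulative duration, dose and their interaction, with threshold models that let the coefficient change. The plan also calls results exploratory where the sample is too small, and the reassurance sentence is Discussion text rather than a decision rule. All of this is fair. But a threshold model learns little from a sparse range, and the exploratory clause is not tied to duration. The Discussion sentence is also the only reading of a null that the article gives, and it is addressed to patients and guidelines.

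**Conclusion.** The concern holds in limited form. The planned reading of a null result has no duration limit, while use beyond 10 years is limited in the Australian cohorts and very thin in Rotterdam. Under even starts with no stopping or death, it is about 1-5% of exposed time in Rotterdam, 2-5% in the Australian cohorts to 2018, and 11-16% to an assumed 2022. About 28-49% of exposed time lies beyond 5 years. These shares rest on assumed initiation, persistence and data-end dates, because the article gives no rates and no Australian end date; ignoring stopping and death favours the plan. It is not shown that the main analysis would miss a late effect, only that it could, and that nothing stated guards against reading such a null as reassurance.

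**What to change.** 1. Alongside the dose-duration model, report person-years, events and the estimate with its confidence interval for <5, 5-<10 and >=10 years of cumulative CCB use.
2. Reword the closing paragraph of the Discussion so that a null conclusion covers only the durations observed. Make any reassurance about long-term use conditional on the upper confidence limit for >=10 years excluding an increase stated in advance.
3. Show the planned analysis with prior CCB users, and any earlier-entry analysis, beside this table as supporting evidence. State the prevalent-user selection that the former brings. Neither should become the designated analysis for long use: adding prior users brings back the selection that the exclusion was meant to avoid.

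The cost is one added table, some wording, and a narrower conclusion if the result is null. No new data are needed.
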